#### Quality Adjusted Life Years (QALYs)

Preference-based quality of life scores will be obtained by administering the EQ-5D to all patients in both the control group and the two intervention groups at baseline, 4.5 months of follow-up, and 9 months of follow-up. QALYs will subsequently be estimated by calculating the area of the two trapezoids that result from linear extrapolation of the three quality of life scores.

#### Cost-effectiveness

The balance between costs and effects will be assessed by estimating the incremental cost per QALY gained (ICER) for the intervention group compared with the control group.

The time horizon over which the costs end effects of the different treatment strategies will be compared is equivalent to that observed during the period of the study (i.e. no future projections will be made). Uncertainty surrounding the ICER will be represented through the use of cost-effectiveness acceptability curves, which show, for each possible value of λ (i.e. the societal willingness-to-pay for one additional QALY), the probability that the intervention will be cost-effective.

### Randomisation and data collection

Patients can be randomised during admission for HF, and in case of worsening of HF at the outpatient clinic. After confirmation of eligibility and written informed consent, patients will be included into the study. Patients will be randomised into the control or intervention group. Patient characteristics and clinical variables will be collected at baseline, and 2 weeks and 9 months after discharge. Echocardiography, ECG, and laboratory analysis will be performed at baseline during hospitalisation and at the end of the study. Quality of life as part of the primary endpoint, measured with the Minnesota Living with HF Questionnaire, will be collected at baseline and at 9 months. Data about utilisation of resources will be collected prospectively and comprise components of direct costs, i.e. scheduled and non-scheduled outpatient visits and hospital admissions.

Questionnaires about self-care behaviour, anxiety, depression, compliance and medical technology assessment (MTA) will be completed before discharge, and at 4.5 and 9 months (Table 3). Patients should be included preferably as soon as possible but at least within a period of time of 14 days after discharge or after the first visit at the HF clinic with worsening HF.

**Table 3 T3:** Questionnaires and medical assessment used in the IN TOUCH

*Questionnaires *	Baseline	2 weeks	4,5 month	9 month
Minnesota Living with Heart failure Questionnaire (MLHFQ)	•			•
Revised Heart failure Compliance	•			•
Disability Rating Index (VAS)	•			•
Hospital Anxiety and Depression scale (HADS)	•			•
Heart failure self-care behaviour scale (EHFScB)	•			•
Medical technology assessment (MTA)			•	•
EQ-5D	•		•	•
Satisfaction questionnaire for patients and providers				•
***Medical assessment***				
NYHA score	•	•		•
Echocardiography	•			
ECG	•	•		•
Physical examination	•	•		•
Laboratory tests	•	•		•

### Control group

#### ICT guided disease management system without telemonitoring

Patients in this group receive care guided by an ICT DM system. This system supports DM in a fully automatic way, assisting the HF nurse to optimise pharmacological and non-pharmacological treatment, evaluate treatment and adjust therapy to optimal levels, according to current HF guidelines. The patient will receive tailored education and counselling on the HF regimen, symptom management and improvement of the pharmacological and non pharmacological regimen.

The system mainly works as a computer decision support system. Based on the input of data from physical examination, medical history, questionnaires and nursing assessment, the system provides an advice to healthcare providers according to the actual guidelines, including up titration of HF medication to optimal doses.

### Intervention group

#### ICT guided disease management with telemonitoring

Patients in the DM with telemonitoring group will be treated with the above described ICT guided DM system in combination with the following integrated telemonitoring devices that will be installed at the patients' home;

• weighing scale; patients will be instructed to weigh daily.

• blood pressure meter; patients will be instructed to measure their blood pressure daily during up titration of medication.

• ECG; patients have to perform an ECG twice a week during up titration of beta-blockers.

• Health monitor; an interactive monitor collects data from the weighing scale, blood pressure meter and ECG device and will respond to the patients' collected data. Data will be directly transmitted to the DM system in the hospital.

In case of a deviation of individualised predefined ranges of weight, blood pressure or heart rhythm, the health monitor will automatically generate supplementary questions directly to the patient to evaluate the actual health situation. This data, measurements and subjective patient information (predefined multiple choice questions about HF symptoms) will be transferred to the computerised DM in the hospital. Furthermore, the health monitor will generate an advice about the non-pharmacological treatment, for example regarding compliance with fluid and sodium restriction. When the data collected by the system deviates from predefined ranges, the HF nurse will be informed automatically by mobile phone and email. In that case, the HF nurse will contact the patient by phone within two hours and further discusses symptoms and treatment. If data are outside any reference range in combination with symptoms of deterioration, patients will receive a message from the health monitor that they will be contacted by the HF nurse.

### Sample size calculation

Group sample sizes of 130 patients for the group treated with telemonitoring and ICT guided DM and 90 patients treated with ICT guided DM achieve 80% power to detect superiority for telemonitoring using a one-sided, two-sample t-test. The margin of equivalence is 0.0. The true difference between the means is assumed to be 0.8. The significance level (alpha) of the test is 0.025. The data are drawn from populations with standard deviations of - 2.0 and + 2.0. These figures are based on a publication [37] in which the effect of the combination of isosorbidedinitrate and hydralazin was investigated in patient with HF. In this study a difference of 0.4 was demonstrated regarding the composite endpoint. Using telemonitoring, we expect to find a larger difference especially in the QoL domain. It has to be addressed that no information is currently available regarding the sensitivity of the composite endpoint in a setting of new onset or worsening HF patients.

### Statistical analyses

The primary analysis will consist of a comparison of the composite endpoint scores (Table 2) between ICT guided DM in combination with telemonitoring, compared to ICT guided DM without telemonitoring. The test will be performed using a two-sample t-test, and two-sided 95% confidence intervals will be constructed to describe the treatment differences. An analysis of covariance will be used to test for the treatment effect controlling for different baseline characteristics. The results will be analysed using an intention-to-treat analysis including the full set of all randomised patients (primary efficacy population). The primary efficacy population will be analysed at endpoint for composite score. Secondary endpoints involving e.g. individual evaluation of deaths, hospitalisations, and QOL after 9 months will be analysed over the entire course of the study using appropriate methods. Two types of economic analyses will be performed: these include a cost-consequence analysis (CCA) for a disaggregated examination of resource costs and health outcomes associated with the alternative intervention; and cost-effectiveness analysis (CEA) in which the alternative intervention is examined in light of total cost per unit of health outcome. Thus CCA will be performed using the primary outcome of the study as the measure of effectiveness. For this, the annual cost per patient treated to postpone or prevent one patient experiencing a cardiovascular death or hospital admission for worsening HF within the trial will be calculated [38]. For CEA, the incremental cost-effectiveness ratios (ICERs), in terms of cost per life year gained (LYG), will be estimated given that there was a significant increase in survival with DM and telemonitoring. CEA will not be performed in case no reduction will be observed in cardiovascular or all cause mortality. In case of missing data for the composite end point score, the worst-case scenario will be assumed for the primary analyses. Patients lost to follow-up will be assumed to have died (-3) and those without a quality of life measurement will be assigned the worst score (-2).

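### The headline t-test leaves out baseline MLHFQ, although the score contains change from that baseline; making the planned ANCOVA primary would gain modest precision at almost no cost

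*Protocol article*

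**What the plan says.** Under Statistical analyses, the primary analysis compares the composite scores of the two arms: "The test will be performed using a two-sample t-test, and two-sided 95% confidence intervals will be constructed to describe the treatment differences". The next sentence adds an adjusted analysis: "An analysis of covariance will be used to test for the treatment effect controlling for different baseline characteristics". The article does not name the covariates or say how this ANCOVA ranks against the t-test.

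Under Primary endpoint, Table 2 adds three parts: death (-3), first HF readmission (-1), and change in MLHFQ at 9 months, scored from +2 to -2 in fixed bands of absolute change. The top two bands need improvements of at least 20 units and of 10 to 19 units. Randomisation and data collection (text and Table 3) places the MLHFQ at baseline and at 9 months.

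The Sample size calculation rests on the same unadjusted test. It says that 130 and 90 patients "achieve 80% power to detect superiority for telemonitoring using a one-sided, two-sample t-test", and gives the other inputs as "The true difference between the means is assumed to be 0.8", "The significance level (alpha) of the test is 0.025" and "The data are drawn from populations with standard deviations of - 2.0 and + 2.0".

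For the economic evaluation, EQ-5D is taken at baseline, 4.5 and 9 months, and "QALYs will subsequently be estimated by calculating the area of the two trapezoids that result from linear extrapolation of the three quality of life scores".

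**The concern.** A change score depends on where the patient starts. If the MLHFQ scale starts at zero (the article does not give its range), a patient with a baseline below 20 cannot earn +2, and one below 10 cannot earn +1. Baselines will also vary, because patients may enter during an admission, at an outpatient visit with worsening HF, or up to 14 days after discharge. Quality of life spans four of the eight points of the composite, and the Sample size calculation expects the larger effect especially in that domain. Baseline MLHFQ is therefore a natural prognostic covariate, and the primary test does not use it.

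At stake is the width of the headline interval and a few points of power. The unadjusted estimate also moves with any chance baseline difference between arms, whereas an adjusted estimate would largely remove that movement.

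The QALY estimate has a related feature: the area under the EQ-5D curve includes the baseline value, which treatment cannot have affected.

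**Working it through.** **Inputs from the Sample size calculation.** n = 130 and 90; difference 0.8; SD 2.0 in each arm (printed with minus and plus signs); one-sided alpha 0.025; margin zero, so plain superiority.

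**Step 1: the plan's own figure.**
- Standard error = 2.0 × √(1/90 + 1/130) = 2.0 × 0.1371 = 0.274.
- Noncentrality = 0.8 / 0.274 = 2.92.
- Power from the noncentral t with 218 degrees of freedom = **82.7%** (83.1% by the normal approximation). The article states 80%.
- About 206 patients (84 + 122) would give 80% by the normal approximation, so 220 is sufficient without adjustment.

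**Step 2: effect of adjusting for baseline MLHFQ.** With correlation r between baseline MLHFQ and the composite, the residual SD is 2.0 × √(1 − r²). The half-width is 1.971 × residual SD × 0.1371. The equivalent gain in patients is 220/(1 − r²) − 220.

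| Assumed r | Residual SD | Power | 95% CI half-width | Equivalent extra patients |
|---|---|---|---|---|
| 0 | 2.00 | 82.7% | 0.54 | 0 |
| 0.10 | 1.99 | 83.1% | 0.54 | 2 |
| 0.20 | 1.96 | 84.2% | 0.53 | 9 |
| 0.25 | 1.94 | 85.1% | 0.52 | 15 |
| 0.30 | 1.91 | 86.1% | 0.52 | 22 |
| 0.35 | 1.87 | 87.3% | 0.51 | 31 |

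**Step 3: is that range of r plausible?** The documents give no r, so Table 2 was simulated with assumed inputs:
- 10% deaths, each also given the worst quality-of-life score, and 25% readmissions;
- a 0–105 scale with mean baseline 35–55 and SD 18–22;
- a mean improvement of 10 units;
- a baseline-to-9-month correlation of 0.3–0.7.

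The resulting r was 0.21 to 0.34 (r² of 4–12%), with a score SD of 2.0 to 2.2, close to the plan's 2.0. Varying mortality over 5–15% as well widens r to roughly 0.17–0.42. The simulation made death and readmission independent of baseline MLHFQ. If patients with worse baselines also die or return more often, that works against their greater room to improve, and r would be smaller.

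**Step 4: chance imbalance.** A baseline difference of two standard errors shifts the unadjusted difference by r × 2 × 0.274. That is 0.11 points at r = 0.20 and 0.19 at r = 0.35, or 14–24% of the assumed 0.8.

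**Step 5: QALY weights.** Each trapezoid spans 4.5 months = 0.375 years, so the baseline value has weight 0.375/2 = 0.1875 years, the 4.5-month value 0.375 and the 9-month value 0.1875. As an illustration only, a baseline EQ-5D difference of 0.05 would add 0.05 × 0.1875 = 0.009 QALY whatever the treatment does.

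**The case against.** The strongest reply is that nothing here is an error. Under randomisation the t-test is unbiased and controls type I error. Chance imbalance is already reflected in its standard error. It is the test used for sizing, and it exceeds the stated power. All of that stands.

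Several stronger readings are tempting, and the documents do not support them:

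- **That the available precision is thrown away.** An ANCOVA for the treatment effect is already planned. Precision is forgone only in the headline test.
- **That baseline MLHFQ determines the composite.** The scores for death and readmission do not depend on it arithmetically, and a missing quality-of-life measurement receives -2 whatever the baseline.
- **That covariates will be picked after seeing imbalance.** The word used for the baseline characteristics may simply mean various. An article commonly leaves the covariate list to the full protocol or analysis plan, so its absence is not a finding.
- **That imbalance in MLHFQ reaches the cost-effectiveness ratio.** It does not. QALYs come from EQ-5D, and the cost-effectiveness analysis under Statistical analyses uses life years gained.
- **That the trial has no power to spare.** Under its own inputs it has 82.7%. Whether 0.8 is optimistic is a separate question.

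The reply does not remove the remaining point. The article itself fixes the unadjusted test as primary while planning an adjusted one, and the covariate most closely tied to the endpoint is collected in any case.

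**Conclusion.** The point holds as a modest gain in efficiency. The primary test is valid and adequately powered as planned, but it is not the most precise analysis of a score that contains a banded change from a measured baseline. For an assumed r of 0.2 to 0.35, adjustment adds about 1.5 to 4.6 points of power and shortens the interval by 2–6% (1 − √(1 − r²)). At r = 0.1 the gain is negligible. The size rests wholly on the assumed r, which the documents do not supply.

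The QALY limb is secondary. The weight of 0.1875 years is exact, but the 0.05 imbalance is illustrative, and adjustment for baseline EQ-5D may already be set out in a fuller plan that is not shown.

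**What to change.** - Make the ANCOVA the single primary analysis: composite score on arm and baseline MLHFQ, with baseline MLHFQ named in advance. Inclusion setting (inpatient or outpatient) is an optional second covariate.
- Report the adjusted difference with its two-sided 95% confidence interval, and keep the unadjusted t-test as supportive.
- State a rule for a missing baseline MLHFQ, so that every randomised patient stays in the model as the intention-to-treat analysis requires.
- Estimate the QALY difference by regression on arm and baseline EQ-5D.

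The cost is a change of wording, made before the comparison of the arms is seen; no new data are needed. The slight downside is that the primary analysis no longer matches the sizing test exactly. The sample size need not be recalculated, because the unadjusted design already reaches 80%.

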### Aim of the study

The primary aim of this study is to assess the effect of telemonitoring on top of an ICT guided DM system in patients after worsening HF on the combined endpoint of death, readmission and quality of life, compared to patients treaded with ICT guided DM alone.

Secondary aims of the study are;

• To assess the effect of telemonitoring in addition to an ICT guided DM system compared to an ICT guided DM alone on the separate components of the combined endpoint (death, readmission and quality of life).

• To determine the cost benefit ratio of ICT guided DM with telemonitoring compared to ICT guided DM alone.

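### The article contradicts itself on the cost-effectiveness analysis: cost per QALY without condition in one section, cost per life year dependent on survival, by two different rules, in another

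*Protocol article*

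**What the plan says.** **Aim of the study** lists among the secondary aims: "To determine the cost benefit ratio of ICT guided DM with telemonitoring compared to ICT guided DM alone". Secondary endpoints repeats the cost-benefit ratio. Neither attaches a condition.

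**Quality Adjusted Life Years (QALYs)**: "Preference-based quality of life scores will be obtained by administering the EQ-5D to all patients", at baseline, 4.5 and 9 months.

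**Cost-effectiveness**: the balance of costs and effects "will be assessed by estimating the incremental cost per QALY gained (ICER) for the intervention group compared with the control group". The horizon is the study period, and "Uncertainty surrounding the ICER will be represented through the use of cost-effectiveness acceptability curves". No survival result is required.

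**Statistical analyses** promises two economic analyses, a cost-consequence analysis (CCA) and a cost-effectiveness analysis (CEA), and defines the CEA broadly as total cost per unit of health outcome. The CCA carries no condition. For the CEA, the ICER is expressed per life year gained and "will be estimated given that there was a significant increase in survival with DM and telemonitoring". The next sentence adds: "CEA will not be performed in case no reduction will be observed in cardiovascular or all cause mortality". QALYs are not mentioned in this section.

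**The concern.** Three things do not fit together.

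1. The unit of the ICER is the QALY in one section and the life year in the other.
2. The ICER is unconditional in one section and conditional on survival in the other.
3. The condition is given twice, differently. A significant gain and an observed reduction are separate rules. The second names cardiovascular or all-cause mortality without saying what happens if they disagree.

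The condition is also unsound in itself. An economic evaluation concerns cost and effect jointly, and an acceptability curve already expresses the uncertainty without a prior test. Sample size calculation says the larger effect is expected mainly in quality of life. A mortality condition would therefore withhold the ICER in the situation the sponsor thinks likely. It would also withhold it if telemonitoring added cost without saving lives, which a payer needs to know. ICERs reported only after a favourable mortality result come from a selected set of outcomes and lean towards telemonitoring. While the text is unreconciled, the choice of rule could follow the mortality result.

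**Working it through.** **The plan's own figure.** The only power stated is 80% for the composite score (difference 0.8, SD 2.0, 130 v 90, one-sided 0.025). Recomputed: 0.8 / (2.0 × √(1/90 + 1/130)) = 0.8 / 0.274 = 2.92, and Φ(2.92 − 1.96) = 83% (82.7% with the t distribution). This is slightly above the stated value and has no bearing here. No power is given for mortality.

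**Inputs.** Group sizes of 90 (control) and 130 (intervention) come from Sample size calculation. Control mortality of 10%, 15% or 20% at 9 months and relative reductions of 30% or 40% are assumptions, because the article gives neither.

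**Significance rule.** Two-sided 0.05, two proportions. The smallest significant gap is g = 1.96 × √(p̄(1 − p̄)(1/90 + 1/130)), with p̄ the pooled rate. Power = Φ((p_c − p_t − g) / √(p_c(1 − p_c)/90 + p_t(1 − p_t)/130)).

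Example, 15% v 10.5%: p̄ = (13.5 + 13.65)/220 = 0.123; g = 1.96 × √(0.123 × 0.877 × 0.0188) = 0.088; power = Φ((0.045 − 0.088)/0.0463) = Φ(−0.94) = 17%.

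**Observed-reduction rule.** The exact probability that the observed death proportion is lower with telemonitoring: sum Bin(x; 90, p_c) × Bin(y; 130, p_t) over all x, y with x/90 > y/130. This treats the rule as applying to a single mortality measure.

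| Control v intervention | CEA runs: significant gain | CEA runs: observed reduction |
|---|---|---|
| 10% v 7% | 13% | 78% |
| 10% v 6% | 20% | 86% |
| 15% v 10.5% | 17% | 83% |
| 15% v 9% | 29% | 91% |
| 20% v 14% | 22% | 88% |
| 20% v 12% | 37% | 94% |
| no effect (10-20% in both) | 2.5% | about 49% |

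The analysis would be skipped in 63-87% of trials under the first rule and in 6-22% under the second, if telemonitoring does reduce deaths by 30-40%.

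**Selection.** Smallest significant gap against the true gap:
- 10% v 7%: p̄ = 18.1/220 = 0.082, g = 7.4 points, 7.4/3.0 = 2.5
- 15% v 10.5%: g = 8.84 points, 8.84/4.5 = 1.96
- 20% v 12%: p̄ = 33.6/220 = 0.153, g = 9.7 points, 9.7/8.0 = 1.2

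Every trial that passes the significance rule in these scenarios shows a larger mortality difference than the true one, by a factor that depends heavily on the assumed rates. Selection is much milder under the observed-reduction rule.

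**The case against.** The best defence is a narrow reading. The significance condition is attached to the ICER per life year gained, and withholding that ratio when no life years are gained is understandable, because it is then undefined or negative. On this reading the cost per QALY survives untouched. The reading is possible, but the text does not secure it. The second sentence cancels the CEA as a whole, the same section defines CEA as cost per unit of health outcome, and the QALY plan sits under the heading Cost-effectiveness. The documents leave the matter open, so one cannot treat the QALY analysis as cancelled or as safe.

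A reader might also infer more than the article supports:

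- *That a secondary aim is all but cancelled.* The aim is a cost-benefit ratio, and the unconditional CCA would still give a cost per cardiovascular death or heart failure admission prevented. Savings through fewer admissions would be visible there. What is at risk is the ICER.
- *That the trial would most likely report no ICER.* That holds under the significance rule only. Under the observed-reduction rule, with the same assumptions, the CEA would usually run.
- *That any reported ICER would rest on a mortality effect at least twice the truth.* The factor is 1.96 at 15% v 10.5% and 1.2 at 20% v 12%, and it concerns the stricter rule.

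It is also fair that this is a secondary analysis. The primary endpoint, its test and the data collection are untouched.

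**Conclusion.** The contradiction stands on the page and needs no outside figure: two units for the ICER, an unconditional and a conditional plan, and two different conditions. Making the analysis depend on mortality is a poor choice under either rule, given where the benefit is expected and the selective reporting that follows.

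The size of the consequence depends on which sentence governs, which the article does not settle: the CEA would run in about 13-37% of trials under one rule and 78-94% under the other. These ranges rest on assumed control mortality of 10-20% and a 30-40% reduction. With no mortality effect the figures are about 2.5% and 49%. The point should be fixed, but it does not threaten the trial's primary conclusion or the CCA.

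**What to change.** In Statistical analyses, delete both survival conditions. State that the incremental cost per QALY over the 9-month study period, as set out under Quality Adjusted Life Years and Cost-effectiveness, is always reported with the acceptability curve already planned there. Present any cost per life year gained as secondary, and likewise not dependent on the mortality result. Leave the cost-consequence analysis as it is.

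The cost is a few lines of wording. EQ-5D, survival and resource-use data are already planned for collection, and no added patients or visits are needed. The change should be made before comparative results are seen, so that the rule cannot be chosen in their light.
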